#### Health economic evaluation

The objective of the health economic evaluation is to determine the efficacy of the intervention by comparing cost and outcome of the intervention group with cost and outcome of the control group (care as usual). All costs associated with the intervention as well as costs resulting from the consumption of health-related goods and services [45] will be considered from the perspective of the German social insurance (statutory health insurance, long-term care insurance, and pension insurance).

In order to determine the efficacy of the intervention, a cost-effectiveness analysis in terms of additional costs per additional hospital admission averted and a cost–utility analysis, which aims to calculate the additional costs required for an improvement in QALYs, will be performed. While the former yields the incremental cost-effectiveness ratio (ICER), the latter estimates the incremental cost-utility ratio (ICUR). The QALYs are based on health-related quality of life, which will be measured by the EQ-5D-5L and evaluated by a German tariff [46] to generate utilities. ICER and ICUR are calculated similarly as the ratio of the difference in mean costs and difference in mean outcomes between intervention and control group. Both costs and outcomes will be derived from cluster averages.

Statistical analyses will be based on the intention-to-treat principle. A 95% confidence interval will be obtained parametrically for the ICER/ICUR and non-parametrically by a bootstrap procedure [47, 48]. Univariate and probabilistic sensitivity analyses will be performed to estimate the robustness of the ICER/ICUR.

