### Secondary outcomes

The following secondary outcomes will be analysed on the basis of data collected by study nurses during home visits at baseline and after 6 and 12 months:
Total number of medications, Drug Burden Index defined as the number of anticholinergic and sedative medications [16], prevalence of potentially inappropriate medications (PIMs) [35, 36], medication regimen complexity [37], and drug–drug interactionsWeakness measured by grip strength using a dynamometer (model SH5001; Saehan Corp., Masan, Republic of Korea); best of three attempts usedCognition: Two short cognitive subtests from the Consortium to Establish a Registry for Alzheimer’s Disease neuropsychological test battery, German version, with norms and reliable change indices recently derived from an older German GP sample [38, 39]:
◦ Episodic memory: word list learning (three trials immediate and one trial delayed recall); total administration time: maximum of 10 min plus 10-min interval and approximately 30 s for instruction◦ Executive function: semantic fluency (animal naming test) as a measure of combined verbal ability and executive control; administration time 1 min plus approximately 20 s for instructionDepressive disorder assessed by the Geriatric Depression Scale [40]Mobility measured by the Timed Up & Go Test [41]Health-related quality of life (EQ-5D-5L) will be assessed to facilitate calculation of quality-adjusted life-years (QALYs) for use in the economic analysis [42].Activities of daily living measured by the Barthel index [43]Weight (self-reported)Number of falls (self-reported)Use of emergency services

Detailed procedures of the measurements are listed in the schedule of enrolment, interventions, and assessments (Table 1).

**Table 1 Tab1:** Adapted SPIRIT schedule of enrolment, interventions, and assessments

	Study period						
	Enrolment	Baseline	Intervention				Close-out
Time point	**− t**_**1**_	**t**_**0**_			**t**_**1**_		**t**_**2**_
Month	− 3	0	1	3	6	9	12
Enrolment							
Eligibility screen	X						
Informed consent	X						
Allocation		X					
Interventions							
Intervention group (family conferences)			X	X		X	
Control group (care as usual)							
Assessments							
Hospitalisation rate (NHPP)					X		X
Medication (TNM, DBI, PIM)		X			X		X
Grip strength		X			X		X
Cognition (CERAD)		X			X		X
Depression (GDS)		X			X		X
Mobility (Timed Up & Go Test)		X			X		X
Health-related quality of life (EQ-5D-5L)		X			X		X
Activities of daily living		X			X		X

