### Sample size

In a similar trial population, the mean rate of hospitalisations amounted to 0.38 per patient with a standard deviation of 0.75 during 6 months [44]. We assume that during an observation period of 12 months, the mean number of hospitalisations per patient will be 0.75 with a common standard deviation of 1.0, and we expect a decrease to a mean number of 0.5 in the intervention group. With a power of 80% and an alpha error of 0.05, we would need a sample size of 253 in each group (two-sided *t* test for equal variances) to detect the expected difference. For a cluster randomised intervention trial, the estimated sample size must be adjusted by the design effect. If an intra-cluster correlation of 0.05 is assumed and about five patients per GP are planned, the design effect would be 1.2 and the sample size would be 608 patients in 122 GP practices. With an estimated drop-out rate of 10% during the study period, 676 patients and 136 GPs will be needed in total.

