### Data analysis

#### Statistical analyses

The analysis of the primary endpoint will be conducted according to the intention-to-treat principle. Sensitivity analyses will be performed on the basis of the per-protocol population (i.e., all patients who have finished the study without any protocol violations will be included in these analyses). Missing values will not be imputed *a priori*. To evaluate a possible bias due to values that are not randomly missing, sensitivity analyses based on multiple imputation will be performed.

Due to cluster randomisation, hierarchic multilevel models (mixed models) with GP practice as a random effect will be applied for the analyses of primary and secondary endpoints. Possible baseline imbalances and confounding variables (e.g., age, sex, co-morbidities) will be controlled by adjustment.

For the evaluation of the primary endpoint, a linear mixed model analysis of variance will be applied.

The analyses of the secondary endpoints will be performed by using linear mixed models or mixed logistic regression models (binary or ordinal), depending of the underlying distribution of the outcome variable.

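### The incremental QALY in the cost-utility ratio is a difference in arm means with no baseline-utility covariate, which gives up precision that the collected EQ-5D-5L data could supply

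*Protocol article*

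**What the plan says.** The Health economic evaluation section defines both ratios in one sentence: they are "calculated similarly as the ratio of the difference in mean costs and difference in mean outcomes between intervention and control group". The next sentence sets the level of summary: "Both costs and outcomes will be derived from cluster averages". QALYs rest on quality of life "measured by the EQ-5D-5L and evaluated by a German tariff". The section restates intention-to-treat, plans parametric and bootstrap confidence intervals, and adds that "Univariate and probabilistic sensitivity analyses will be performed to estimate the robustness of the ICER/ICUR". It names no regression and no covariate.

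Under Secondary outcomes, EQ-5D-5L "will be assessed to facilitate calculation of quality-adjusted life-years (QALYs) for use in the economic analysis", and it belongs to the "data collected by study nurses during home visits at baseline and after 6 and 12 months". Table 1 marks the same three visits. A pre-intervention utility is therefore scheduled for every patient in both arms.

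The Statistical analyses section assigns mixed models with practice as random effect to the primary and secondary endpoints and continues: "Possible baseline imbalances and confounding variables (e.g., age, sex, co-morbidities) will be controlled by adjustment". The economic section does not repeat or refer to that sentence.

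**The concern.** A QALY computed from visits at 0, 6 and 12 months normally contains the baseline utility itself, and later utilities tend to follow it. If the arms differ at baseline by chance, part of that difference reappears in the incremental QALY as if the intervention had produced it. Randomisation is by blocks of practices, and no balancing on utility is stated.

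The incremental QALY is the denominator of the ICUR, so a small shift there can change the size or sign of the ratio. The article's Discussion links a positive evaluation to possible payment for family conferences by statutory health insurance, so the economic result may carry weight. Baseline utility is also likely to be the strongest single predictor of the QALY, and leaving it out widens the uncertainty for no saving.

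**Working it through.** **The plan's own figure.** The article gives no precision for QALYs; its only sample-size figure is for hospitalisations. It assumes that "the mean number of hospitalisations per patient will be 0.75 with a common standard deviation of 1.0", with 0.5 expected under intervention. A two-sided t test at 80% power gives 253 per arm, which reproduces. The design effect is 1 + (5 − 1) × 0.05 = 1.2. Then 506 × 1.2 = 607.2 (stated 608), and 608 / 0.9 = 675.6 (stated 676). I take 608 / 2 = 304 analysed patients per arm and the design effect of 1.2 from here. The latter is borrowed from the hospitalisation endpoint.

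**Assumptions that the article does not supply.** QALY = 0.25·u0 + 0.5·u6 + 0.25·u12 (area under the curve); utility SD s = 0.25 (range 0.20–0.30), equal at each visit; between-visit correlation r = 0.5 (range 0.3–0.7).

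**Without deaths.**
- Pass-through of a baseline difference = 0.25 + 0.75r: 0.475, 0.625 and 0.775 at r = 0.3, 0.5 and 0.7.
- Var(QALY)/s² = 0.375 + 0.625r: 0.5625, 0.6875 and 0.8125.
- R² = (pass-through)² / [Var(QALY)/s²]: 0.40, 0.57 and 0.74.
- SE of the baseline utility difference = s·√(2 × 1.2 / 304) = 0.022 at s = 0.25 (0.018–0.027 over the SD range).
- At r = 0.5, a one-SE imbalance shifts the incremental QALY by 0.625 × 0.0222 = 0.014. The unadjusted SE is √0.6875 × 0.0222 = 0.018; adjusted it is 0.018 × √(1 − 0.568) = 0.012.

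**With deaths scored as zero.** The patients are frail and aged 70 or older, so some will die within the year. Assume 12-month mortality m, unrelated to baseline utility or arm, half of it before month 6, and mean utility μ among the living. Put a = 1 − m/2, b = 1 − m, k = μ²/s².
- Pass-through = 0.25 + 0.5·a·r + 0.25·b·r.
- Var(QALY)/s² = 0.0625 + 0.25·[a + a(1 − a)k] + 0.0625·[b + b(1 − b)k] + 0.25·a·r + 0.125·b·r + 0.25·[b·r + b(1 − a)k].
- Example, m = 0.10, μ = 0.6, r = 0.5: a = 0.95, b = 0.90, k = 5.76. Pass-through is 0.60, the variance term 0.809, R² = 0.36 / 0.809 = 0.44. The SE goes from 0.020 to 0.015.
- Least favourable corner (m = 0.20, μ = 0.7, r = 0.3): pass-through 0.445, R² 0.22.
- Most favourable corner with deaths (m = 0.05, μ = 0.6, r = 0.7): pass-through 0.76, R² 0.66.

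**Summary over the ranges.**

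| | Pass-through | R² | Adjusted / unadjusted SE, √(1 − R²) |
|---|---|---|---|
| No deaths | 0.475–0.775 | 0.40–0.74 | 0.77–0.51 |
| Deaths as zero | 0.445–0.76 | 0.22–0.66 | 0.88–0.58 |

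The design effect cancels from pass-through and R² if clustering is similar for baseline utility and QALY. The R² values carry over to a regression on practice means if the correlations are similar between and within practices.

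**The case against.** The strongest reply is that the text never uses the word unadjusted. A ratio of mean differences is the generic definition of an ICUR, an adjusted mean difference is still a mean difference, and cluster averages fix a level of summary without forbidding covariates. A health economic plan that is not shown might add them, and the adjustment sentence under Statistical analyses has an open list of examples. This stands in part: nothing excludes adjustment, and the fix can keep the cluster-average level. But the article does state how the ratio is formed, in its own subsection and without a covariate. The adjustment sentence is attached to the primary and secondary endpoints. EQ-5D-5L is among those endpoints; the ICUR is not. The bootstrap and the sensitivity analyses describe sampling and parameter uncertainty and do not remove a realised imbalance.

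Three stronger readings are tempting, and the documents do not support them.
- A reader might infer that the ICUR is biased. It is not biased by this choice: randomisation makes the difference in mean QALYs unbiased on average, and chance imbalance is part of what the planned intervals are meant to cover. The one-SE shift of 0.014 is smaller than the unadjusted SE of 0.018.
- A reader might infer that the whole imbalance enters the QALY difference. Under the assumptions above, 45–78% does.
- A reader might convert the gain into power. The article states no QALY test and no QALY power; it is sized on hospitalisations. The uncertainty of the ICUR also depends on costs, about which it gives no figures.

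**Conclusion.** The point holds as an efficiency improvement at almost no cost, not as an invalid analysis. As written, the incremental QALY makes no use of a baseline measure scheduled for every patient. Under area-under-the-curve QALYs, about 45–78% of a realised baseline imbalance would carry over. Adjustment would lower the standard error of the incremental QALY by about 23–49% without deaths, and by about 12–42% with deaths scored as zero. Utility SD, correlation, mortality, mean utility and the QALY formula are all assumptions, so the ranges matter more than any single value. The gain remains at the least favourable corner tried, but it is modest there. The effect on the ICUR itself cannot be sized from the article.

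**What to change.** In the Health economic evaluation section, state that the incremental QALY is adjusted for baseline EQ-5D-5L utility. Either of two forms will do:
- a patient-level regression of the 12-month QALY on arm and baseline utility, with GP practice as random effect; or
- a practice-level regression of mean QALY on arm and practice-mean baseline utility, which keeps the cluster-average approach.

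Use the adjusted difference as the ICUR denominator and re-estimate it within each bootstrap replicate, resampling whole practices and keeping each patient's costs and QALYs together. Report the unadjusted difference as a sensitivity analysis. If a separate health economic plan already does this, one sentence aligning the two texts is enough.

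The cost is a short change of wording and a few lines of code. No visit, instrument or patient is added.

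### The planned 95% confidence intervals are placed on the ICER and ICUR, ratios whose intervals can be unbounded or hard to interpret unless the effect difference is clearly non-zero

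*Protocol article*

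**What the plan says.** The Health economic evaluation section of the protocol article plans two ratios. The cost-effectiveness analysis is expressed as "additional costs per additional hospital admission averted", and the cost-utility analysis as "the additional costs required for an improvement in QALYs". Their construction is stated: "ICER and ICUR are calculated similarly as the ratio of the difference in mean costs and difference in mean outcomes between intervention and control group".

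Uncertainty is then attached to the ratios: "A 95% confidence interval will be obtained parametrically for the ICER/ICUR and non-parametrically by a bootstrap procedure". The remaining uncertainty work has the same target: "Univariate and probabilistic sensitivity analyses will be performed to estimate the robustness of the ICER/ICUR".

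The section does not say whether the parametric interval is Fieller or Taylor-series, how the bootstrap limits are formed, or what unit is resampled. For the interval methods it cites two works that are not available here.

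The denominator of the ICER is the between-group difference in hospital admissions, the effect on which the trial is powered. For usual care the Sample size section assumes: "the mean number of hospitalisations per patient will be 0.75 with a common standard deviation of 1.0". The intervention arm is planned at 0.5, so the planned difference is 0.75 − 0.5 = 0.25.

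**The concern.** An interval for a ratio behaves well only when the denominator is clearly away from zero. Otherwise two things happen.

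- **Fieller-type interval.** The 95% set has no finite limits unless the effect difference is itself significant at the two-sided 5% level.
- **Taylor-series or simple bootstrap interval.** The limits are finite, but the ratio does not order results from good to bad. A negative value can mean cheaper and more effective (dominant) or costlier and less effective (dominated). A positive value can mean costlier and more effective or cheaper and less effective. A lower and an upper limit taken across such values have no clear meaning.

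The difficulty arises when the clinical effect is modest, which is when the economic result is likely to be most debated. The Discussion links a positive evaluation to possible payment by statutory health insurance, so the economic result is meant to inform a decision.

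**Working it through.** **1. Inputs (Sample size section).** Control mean 0.75, intervention mean 0.5, common SD 1.0, two-sided 5% test, power 80%, ICC 0.05, about five patients per GP, drop-out 10%.

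**2. The plan's own figures reproduce.**
- A two-sided t test for a difference of 0.25 with SD 1.0 needs 252.1 per group, rounded up to 253.
- Design effect: 1 + (5 − 1) × 0.05 = 1.2.
- 2 × 253 × 1.2 = 607.2, so 608 patients; 608/5 = 121.6, so 122 practices.
- 608/0.9 = 675.6, so 676 patients; 122/0.9 = 135.6, so 136 GPs.

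**3. Precision of the ICER denominator.** There are 608/2 = 304 evaluable patients per arm. Effective number per arm: 304/1.2 = 253.3. SE of the difference in admissions: 1.0 × √(2/253.3) = 0.0889.

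**4. When a Fieller interval is bounded.** Let e be the estimated effect difference and c the cost difference, with standard errors s_e and s_c and covariance s_ce. The 95% set is all R with (c − R·e)² ≤ 1.96² × (s_c² − 2R·s_ce + R²·s_e²). This is a quadratic in R with leading coefficient e² − 1.96²·s_e², and the set is a finite interval only if that coefficient is positive. So |e| must exceed 1.96 × 0.0889 = 0.174 admissions, and P(unbounded) = 1 − power for the effect difference, whatever the costs.

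With d the true difference, power = Φ(d/0.0889 − 1.96) + Φ(−d/0.0889 − 1.96).

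| True difference d | Reduction from 0.75 | d/SE | P(unbounded) | Source of d |
|---|---|---|---|---|
| 0.25 | 33% | 2.81 | about 20% | plan |
| 0.15 | 20% | 1.69 | about 61% | assumed |
| 0.1125 | 15% | 1.27 | about 76% | assumed |
| 0.075 | 10% | 0.84 | about 87% | assumed |

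At d = 0.075 the estimated difference is negative with probability Φ(−0.84) = 0.20. This is a share of trials, not of bootstrap replicates within one trial.

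**5. What a finite interval would look like.** The documents give no cost figures, so this is an illustration only. Assume an observed difference of 0.10 admissions averted, a cost difference of €500, cost SD €10,000, the same design effect and zero correlation. In 100,000 simulated normal draws, 62% were costlier and more effective, 25% cheaper and more effective, 9% costlier and less effective, and 4% cheaper and less effective. The denominator was negative in 13%. The 34% of negative ratios mix dominant with dominated results. The 2.5th and 97.5th percentiles of the ratio were about −€71,000 and +€83,000 per admission averted.

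**6. Net benefit on the same assumed data.** INB(λ) = λ·e − c, with SE = √(λ²·s_e² + s_c²) and s_c = 10,000 × 0.0889 = €889. At λ = €10,000 per admission averted, INB = 1,000 − 500 = €500, SE = √(889² + 889²) = €1,257, and the 95% CI is −€1,963 to €2,963. At λ = 0, €5,000 and €20,000 the intervals are −€2,242 to €1,242, −€1,947 to €1,947 and −€2,394 to €5,394. Each is finite, and a larger value is always better.

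**7. ICUR.** No QALY difference or SD is given. For assumed QALY SDs of 0.15 to 0.30 and the same design effect, P(unbounded) is 68–88% at a true difference of 0.02 and 4–53% at 0.05.

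**The case against.** The strongest reply is that the article does not fix enough detail to be faulted. It names neither a percentile bootstrap nor a Taylor-series interval, and the full protocol or analysis plan may add net benefit, a plane and acceptability curves. The planned bootstrap and probabilistic sensitivity analysis could supply these. This stands in part. A reader might infer that the plan takes percentiles of the ratio, but the text does not say so. The absence of those displays from a condensed article is not a fault either. What remains is the stated choice to place the interval on the ratio.

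A Fieller set always exists, and when unbounded it correctly reports that the data do not determine the ratio. That is true, so it is not a wrong result; it is of little use for a decision. Nor need finite intervals fail on coverage. In simulations with a cost difference of €500, cost SDs of €5,000 to €20,000 and effects of 0.0625 to 0.25, simple percentile intervals covered 96–99%, while Taylor-series intervals ranged from 84% to 99%. The median percentile width ran from about €11,000 to €433,000. For the percentile interval the objection is therefore interpretability and width, not under-coverage.

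Only the 20% figure uses the plan's own effect size; the larger shares rest on assumed smaller effects. Under the design assumption the Fieller interval is bounded in about 80% of trials.

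A reader might also see an error in "Both costs and outcomes will be derived from cluster averages", since the resulting admissions difference can depart from the adjusted mixed-model estimate. The documents do not support that. Cluster summaries are a legitimate way to respect cluster randomisation, and an unadjusted estimate may differ from an adjusted one without either being wrong.

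**Conclusion.** The point holds as a conditional weakness of a stated method. If the effect difference is clearly non-zero, the ratio interval is usable. If not, it is unbounded (Fieller) or finite but hard to interpret (Taylor-series or simple bootstrap).

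For cost per admission averted, the Fieller interval is unbounded in about one trial in five even if every design assumption is met, and more often if the true effect is smaller. These shares rest on a normal approximation, SD 1.0, equal arms of 304 and a design effect of 1.2. The ICUR may also be exposed, since the trial is not powered on QALYs, but the documents give nothing from which to size this.

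A reader might infer that the economic evaluation as a whole is invalid. The documents do not support that: the point estimates and the data are unaffected, and so are the primary endpoint and the sample size. The change should be made because the trial can then answer its economic question whatever the size of the clinical effect.

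**What to change.** In the Health economic evaluation section:

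- Report the ICER and ICUR as point estimates. Add an interval for the ratio only when the joint distribution of cost and effect differences lies essentially in one quadrant.
- Base inference on incremental net monetary benefit, with a cluster-adjusted 95% confidence interval, over a range of willingness-to-pay values for an admission averted and for a QALY.
- Show the cost-effectiveness plane and the acceptability curve from a bootstrap that resamples practices.

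The cost is a change of analysis wording and a little programming on the same data, with no new data collection. The drawback is that results are shown over a range of thresholds instead of as a single interval, and that range, which the article does not give, should be fixed before the data are analysed.

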### Process evaluation

To understand the change process by implementation of the intervention, a comprehensive assessment of process measures alongside the experimental study is indispensable [49]. The process evaluation follows international recommendations for process evaluation of complex interventions [50]. Therefore, different process parameters will be assessed on cluster and individual levels, respectively, with qualitative and quantitative methodological approaches (Table 2).

**Table 2 Tab2:** Elements of the process evaluation

Focus	Documentation/assessment	Measurement point
Feasibility of the intervention	Piloting of family conferences with two physicians/region: **semi-structured telephone interview** with physicians**; semi-structured telephone interview** with patients and relatives	Piloting, prior T_0_
Recruitment procedure of physicians and patients	**Protocol**/region	T_0_
Reasons for non-participation or drop-out	**Structured inquiry and documentation** of reasons	T_0_–T_2_
Description of crucial structure- and process-related factors (CRF) on cluster and patient level	**CRF-baseline data**/cluster and patient	T_0_
Conveyance of the intervention	Mandatory educational sessions: **structured protocol** of each educational session. Use of facultative educational session: **standardised documentation** Use of individual medication reviews in intervention and control group: **standardised documentation**	T_0_ (immediately after the educational intervention) T_0_ T_0_–T_2_
Evaluation of telephone study monitoring of physicians and patients	**Structured protocol**	T_0_–T_2_
Evaluation of training	All participants of the education programme: **Standardised questionnaire** → evaluation of the programme • Attitudes • Acceptance • Self-efficacy • Expectations	T_0_ (after the second education sessions)
Application of training content	All physicians: **semi-structured protocols** evaluation of family conferences • Acceptance • Contents • Duration • Practicability • Need for change	T_0_, after 3 and 9 months (immediately after family conferences)
Experiences of physicians (e.g., attitudes regarding intervention; changes in physician–patient communication; barriers and facilitators)	**Four focus groups**: two/region with 6 to 12 physicians **Guideline-based telephone interviews**: convenience sample of ten physicians/region	T_2_ T_2_
Experiences of families (e.g., consideration of preferences; changes in physician–patient communication; barriers and facilitators)	**Guideline-based telephone interviews**: ten patient–relative dyads/region	After 9 months (immediately after the last family conference)

The recruitment procedure of clusters and patients will be documented, including documentation of the information provided on reasons for non-participation or drop-out. Contextual aspects (e.g., socioeconomic and sociodemographic characteristics of physicians and patients) will be assessed at baseline.

Intervention fidelity will be determined by structured documentation for each education session by the trainers. All participants of the obligatory education sessions will be asked to complete a standardised questionnaire after the second session to evaluate the education programme. The use of the facultative educational elements will be also documented. In addition, telephone study monitoring of physicians and patients will be documented using a structured protocol.

Attitudes and experiences of the physicians related to the COFRAIL intervention, including barriers and facilitators, will be explored through four focus group interviews upon completion of the trial with a convenience sample of 6–12 participants per group. Furthermore, guideline-based telephone interviews will be conducted in a convenience sample of ten physicians per region.

In a subgroup of 20 patient–relative dyads, experiences of families (e.g., consideration of preferences, changes in physician–patient communication, barriers and facilitators) will be assessed after 9 months (immediately after the last family conference) with separate semi-structured telephone interviews.

In addition, medication changes will be analysed for the whole study group, and differences between intervention and control groups will be compared descriptively. A detailed analysis will be performed in a subset of patients to elucidate which recommendations of the deprescribing guideline could be followed and which recommendations were either ignored or proved to be inappropriate. This procedure will allow improvement of the applicability of the guideline.

The process evaluation is purely exploratory. All quantitative data will be analysed descriptively, and the qualitative data will be analysed by content analysis [51] (Table 2).

